**General procedures**															
Written informed consent	X														
Inclusion/exclusion criteria	X														
Demographics	X														
Medical and medication history	X														
**Intervention**															
Randomization		X													
Compliance^b^															
– Asking for compliance			X	X	X	X	X	X	X	X	X	X	X	X	X
– Phone visits												X		X	
– Online check-ups			X	X	X	X	X	X	X	X					
**Psychometric assessment**															
Tics:															
– YGTSS	X	X					X				X		X		X
– ATQ		X					X				X		X		X
– MRVS		X					X				X		X		X
Severity of disease: CGI-S	X	X					X				X		X		X
Improvement of disease: CGI-I							X				X		X		X
Premonitory urges: PUTS		X					X				X		X		X
Quality of life: GTS-QoL		X					X				X		X		X
Mood: BDI-II		X					X				X		X		X
Anxiety: BAI		X					X				X		X		X
ADHD:															
– DSM-IV symptom list		X													
– CAARS		X					X				X		X		X
OCD: Y-BOCS		X					X				X		X		X
**Adverse events**															
Open question							X				X		X		X
**Therapeutic alliance**															
WAI-SR							X				X		X		X

*YGTSS, Yale Global Tic Severity Scale; MRVS, Modified Rush Video-Based Tic Rating Scale; ATQ, Adult Tic Questionnaire; CGI-S, Clinical Global Impression–Severity Score; CGI-I, Clinical Global Impression-Improvement Score; PUTS, Premonitory Urge of Tics Scale; GTS-QoL, Gilles de la Tourette Syndrome-Quality of Life Scale; BDI-II, Beck Depression Inventory; ADHD, Attention Deficit Hyperactivity Disorder; CAARS, Conner’s Adult ADHD Rating Scale; OCD, Obsessive-Compulsive Disorder; Y-BOCS, Yale-Brown Obsessive-Compulsive Scale; BAI, Beck Anxiety Inventory, WAI-SR, Working Alliance Inventory-Short Revised*.

*^a^Booster-sessions: booster-session are optional. Frequency, scope, and number will vary individually in the iCBIT and placebo groups, in the face-to -face CBIT group up to two booster sessions a 60-min between week 11 and 35 are possible*.

*^b^Compliance: the compliance of patients in all treatment arms will be assessed during the telephone and in person visits. In the face-to-face CBIT treatment, arm compliance will also be determined via regular and full participation in the therapy sessions. In the iCBIT and placebo groups, the participation in the therapy session will be determined automatically by the online platform by collecting information on when, how long and where the patients were logged in*.

### Sample Size Calculation

The sample size calculation is based on two studies in which the efficacy of face-to-face CBIT was compared with face-to-face psychoeducation in adult and pediatric patients with TS and chronic tic disorders (6, 7). The average YGTSS–TTS improvement across both studies was 3.5 (±5.5 SD), when comparing face-to-face CBIT to psychoeducation. The basic assumption of our study is that iCBIT is as effective as face-to-face CBIT. However, we expect a mean difference of 3.0 instead of 3.5 for the sample size estimation since only adult patients will be enrolled in this study, and a difference of three points is considered relevant enough to be detectable.

Under these conditions and with a one-sided type I error of 2.5%, *n* = 72 patients per treatment arm are required to reach a power of 90%. Therefore, a total of 144 patients will be included in the Internet-based treatment arms iCBIT and placebo. The expected drop-out rate is considered very low (<10%) based on previous studies in our centers and the studies by Wilhelm et al. (7) and Piacentini et al. (6). But even with as low as 60–65 patients per treatment arm a power of 84–86% can be achieved.

Sample size for the face-to-face CBIT arm in Hannover is feasibility driven. Sixteen patients will be randomized to face-to-face CBIT. The study is not powered for this secondary non-inferiority analysis.

### Data Analysis

The primary outcome measure (YGTSS–TTS) will be used as a continuous variable in the primary statistical analysis. In secondary analyses, YGTSS–TTS and CGI-I will be used as binary covariates for responder analysis: response is defined by a 30% decrease (YGTSS–TTS) and an improvement of 1–2 = much or very much improved (CGI-I), respectively.

#### Primary Analysis

The primary analysis will be performed in the intention-to-treat population. A mixed linear model will be used with change in YGTSS–TTS score (follow-up minus baseline) as the outcome variable. Therapy (iCBIT versus placebo), study site, concomitant tics medications (yes versus no), YGTSS–TTS baseline score, and YGTSS-TTS assessment time point (baseline, week 5, and 1 week after end of treatment) as well as an interaction of therapy and time point will be included as fixed effects in the model. The patient variable will be considered a random effect. The mixed model will be analyzed *via* PROC MIXED procedure in SAS statistical software. The therapeutic effect (iCBIT minus placebo) at week 1 after the end of treatment and the associated two-sided 95% confidence interval will be obtained from this analysis. Superiority of iCBIT will be shown if the upper limit of this confidence interval is less than 0.

Various sensitivity analyses are planned (e.g., in a per-protocol population, using analysis of covariance and more). In the unlikely event that the mixed model will not converge in the primary analysis, an analysis of covariance with last observation carried forward will be carried out instead.

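### The primary mixed model counts baseline as an outcome visit for a change-from-baseline response, which makes the deciding confidence interval too narrow

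*Protocol article*

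**What the plan says.** All of this is in the protocol article, Data Analysis, Primary Analysis, unless noted.

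- **Response:** "change in YGTSS–TTS score (follow-up minus baseline) as the outcome variable".
- **Fixed effects:** therapy, site, tic medication, baseline YGTSS-TTS, and time point with therapy by time. The time factor is given as "assessment time point (baseline, week 5, and 1 week after end of treatment) as well as an interaction of therapy and time point".
- **Covariance:** "The patient variable will be considered a random effect", fitted in PROC MIXED. No other covariance term is named.
- **Decision:** the iCBIT minus placebo contrast one week after treatment (week 11) is taken from this model with its two-sided 95% confidence interval. "Superiority of iCBIT will be shown if the upper limit of this confidence interval is less than 0".
- **Fallback:** if the model does not converge, an analysis of covariance with last observation carried forward replaces it.
- **Reuse:** under Secondary Analyses, the confirmatory non-inferiority comparison with face-to-face CBIT follows the same model.

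**The concern.** The response and the list of time levels do not fit together. Change from baseline is zero at baseline by definition, for every patient and in both arms. Those rows say nothing about treatment, but the model treats them as observations.

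A random patient effect alone gives every visit the same total variance. The model therefore averages a variance of zero with the two real ones and uses the average for the week-11 contrast. The standard error is then too small, and the interval that decides the trial is too short. The target is "with a one-sided type I error of 2.5"%; the actual false-positive rate would be higher. Because the point estimate is not biased, nothing in the output would alert the analyst.

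Two further effects are smaller. The zero rows pull the single baseline slope towards zero, which weakens the covariate adjustment. If the analyst instead used an unstructured covariance and kept the zero rows, the matrix would be singular, and the last-observation-carried-forward fallback could be triggered for an avoidable reason.

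**Working it through.** **Inputs from the article (Sample Size Calculation).** SD 5.5, difference 3.0, one-sided 2.5%, power 90%, 72 per arm in the two Internet arms, dropout below 10%.

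**Inputs not in the article, so assumed and varied.** The ratio of the change variances at week 5 and week 11 (V5/V11), and the correlation between the two changes. The 5.5 is taken as the SD of change at week 11.

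**1. The plan's own figure.** n per arm = 2 × (1.960 + 1.282)² × (5.5/3.0)² = 70.6, so 71 by the normal formula. The t-based calculation gives 72 (power 90.2%). The stated 72 is reproduced. Power at 60 and 65 per arm is 84.2% and 87.0%, close to the stated 84–86%. The sample size is not the problem.

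**2. Closed form, complete data, no covariates.** With a random intercept and therapy by time, the week-11 contrast is the difference in week-11 means. Its true variance is V11 × 2/n. The model uses the average of the visit variances instead:

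- with baseline rows: (0 + V5 + V11)/3
- without baseline rows: (V5 + V11)/2

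For V5 = V11 = 5.5²:

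- true SE = 5.5 × sqrt(2/72) = 0.917
- model SE = 0.917 × sqrt(2/3) = 0.748
- the estimate needed for superiority moves from −1.96 × 0.917 = −1.80 to −1.96 × 0.748 = −1.47
- one-sided error = P(Z > 1.960 × 0.816) = P(Z > 1.600) = 5.5%
- coverage = 100% − 2 × 5.48% = 89.0%

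The same calculation for other variance ratios:

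| V5/V11 | With baseline rows: SE ratio | Coverage | One-sided error | Without: SE ratio | Coverage | One-sided error |
|---|---|---|---|---|---|---|
| 0.5 | 0.707 | 83.4% | 8.3% | 0.866 | 91.0% | 4.5% |
| 0.75 | 0.764 | 86.6% | 6.7% | 0.935 | 93.3% | 3.3% |
| 1.0 | 0.816 | 89.0% | 5.5% | 1.000 | 95.0% | 2.5% |
| 1.5 | 0.913 | 92.6% | 3.7% | 1.118 | 97.2% | 1.4% |
| 2.0 | 1.000 | 95.0% | 2.5% | 1.225 | 98.4% | 0.8% |

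With the baseline rows the interval is nominal only at V5 = 2 × V11, because (0 + 2V + V)/3 = V.

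**3. Simulation of the fitted model under no true effect.**

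- 72 per arm, SD 5.5, correlation 0.6, 20,000 trials per scenario. Equal variances: error 5.4% and coverage 89% with the baseline rows, 2.5% and 95% without. Error with the rows is 6.4% to 7.9% for V5/V11 from 0.75 down to 0.55, and 3.8% at 1.5.
- Adding site, medication and baseline covariates, no dropout, 4,000 to 8,000 trials per scenario. Equal variances: model SE 0.71 against a true 0.84, error 5.3–5.7%, coverage about 90%. Week-5 SD of 4.1 (V5/V11 = 4.1²/5.5² = 0.56): model SE 0.64 against 0.88, error 7.7%, coverage 85%.
- With 8% missing at week 11 and a baseline covariate, 1,500 trials per scenario, equal variances. For correlations from 0.3 to 0.8 the error is 4.9–5.7%. At correlation 0.6 it is 5.1% with the baseline rows and 2.7% without.
- In that last setting with a true difference of 3.0, rejection is 92.9% with the baseline rows and 87.7% without. The gain is spurious.

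**4. How much is due to the baseline rows.** With the week-5 SD at 4.1, dropping the baseline rows but keeping the single random effect still leaves an error of 4.4%. That remainder comes from assuming equal variances at weeks 5 and 11. An unstructured covariance brings it to 2.4%, with 95% coverage.

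**The case against.** **Loose wording.** The bracket may only list the visits at which the YGTSS is measured. A change defined as follow-up minus baseline has no follow-up value at baseline, so the data set may hold no baseline rows. This is possible. But the text gives the three visits as the levels of a factor that interacts with therapy, and nothing in the article excludes the baseline rows or makes the raw score the response. An analyst who follows it literally fits the zeros.

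**Covariance left to the SAP.** PROC MIXED can combine a random effect with a residual structure, and a condensed article need not give one. It is fair that silence on degrees of freedom or residual structure is not an error. The point here rests on what is stated: three time levels, a change response and a patient random effect. A visit-specific structure would not rescue the model either, because the zero-variance row makes an unstructured matrix singular.

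**Size depends on unknown variances.** This stands. The article gives one SD, so no single inflated error rate can be claimed, and the larger figures mix two causes (step 4 of the check). The direction is secure unless the week-5 variance is at least twice that at week 11, which is implausible for an earlier visit.

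**Sensitivity analyses.** A planned analysis of covariance would show a wider interval, but it does not replace the primary decision rule.

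**Conclusion.** The concern holds: the model is wrong as written. With a patient random effect as the only covariance term, the baseline rows shrink the standard error of the week-11 contrast by about 18% when the week-5 and week-11 variances are equal, and the primary test runs at about twice its stated level. If the week-5 variance is half that at week 11, the level is about three times the stated one, part of which comes from the common-variance assumption. These sizes rest on assumed variance ratios.

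The treatment estimate is unbiased and the 72 per arm is unaffected. Non-inferiority is tested only after superiority is shown and uses the same model, so the fault affects both the gate and the test behind it.

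**What to change.** Before unblinding, choose one of two coherent models and state it in the protocol and SAP.

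1. **Change score as response.** Limit the time factor to week 5 and week 11. Keep baseline YGTSS-TTS as a covariate, preferably with baseline by time. Replace the single patient random effect by an unstructured within-patient covariance (REML, Kenward-Roger degrees of freedom). Take iCBIT minus placebo at week 11 from therapy by time.
2. **Raw score as response.** Keep baseline, week 5 and week 11 as time levels, constrain the baseline mean to be equal in both arms, drop the baseline covariate, and use an unstructured covariance.

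Removing baseline from the time levels is the essential step. The unstructured covariance is needed as well if the variances at weeks 5 and 11 differ. Make the same change in the non-inferiority model.

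The cost is a wording change and a few lines of PROC MIXED code, with no extra patients or data. The interval becomes wider and has its stated coverage. The power planned at one-sided 2.5% does not change.

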Therefore, the aim of this study will be to develop and test a fully self-sufficient Internet-delivered CBIT (iCBIT) for adult patients with TS, with no therapist involved in any way (ONLINE-TICS). Although interventions *via* video, Skype, or smartphone have been suggested (11, 17, 18) and, in addition, an RCT started only recently testing the efficacy of a computerized, self-administered version of CBIT (called http://TicHelper.com) in 64 children and adolescents with tics (age 8–18 years) (http://ClinicalTrials.gov Identifier: NCT02413216), to the best of our knowledge, so far, there is no iCBIT program available in any language for the treatment of tics in adult patients with TS and other chronic tic disorders. Since in TS – due to the natural waxing and waning course of tics – it is difficult to demonstrate efficacy of a treatment, only a well-designed and sufficiently powered study is suitable to demonstrate efficacy. Therefore, our study will be a multicenter, prospective, controlled, randomized, observer-blind clinical trial that aims to include 160 patients. ONLINE-TICS will be funded by the Federal Ministry of Education and Research (BMBF) in Germany (BMBF: 01KG1421). It is designed to examine the efficacy of an iCBIT intervention as compared to (1) a placebo platform consisting of psychoeducation only – which is our primary analysis – and (2) a conventional face-to-face CBIT intervention – which is our secondary analysis. We hypothesize that iCBIT (1) is superior to the placebo platform and (2) has a comparable effect size to the face-to-face treatment arm. Planned participating sites are Hannover Medical School (MHH), University of Munich, University of Aachen, University of Lübeck, and University of Dresden.

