### Study Design

This is a multicenter, prospective, randomized, controlled, observer-blind clinical trial on the efficacy of iCBIT in the treatment of tics in adult patients with TS or other chronic tic disorders. For four of the five planned study sites (except for Hanover), a two-armed study design will be used – consisting of a placebo-treatment arm (Internet-based psychoeducation) and an iCBIT-treatment arm. Only in Hannover (MHH), an additional face-to-face CBIT treatment arm will be added. Hannover is the only center offering the face-to-face treatment due to the lack of well-trained therapists in Germany even in centers specializing in TS.

The time from first patient in to last patient out is expected to be 33 months consisting of the recruitment phase (24 months) plus the treatment phase (10 weeks) plus a follow-up (6 months). The drop-out rate is expected to be less than 10%.

This study is registered on ClinicalTrials.gov Identifier: NCT02605902.

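### If the mixed model does not converge, the primary test becomes ANCOVA with last observation carried forward, which is generally biased when dropout differs by arm; an unlikely event, but cheap to fix

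*Protocol article*

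**What the plan says.** The Primary Analysis section sets out the main model: "A mixed linear model will be used with change in YGTSS–TTS score (follow-up minus baseline) as the outcome variable". Its fixed effects include therapy, site, tic medication, baseline score, a therapy-by-time interaction and the "assessment time point (baseline, week 5, and 1 week after end of treatment"). Patient is a random effect, and no other covariance structure is named. Superiority is shown if the upper limit of the two-sided 95% confidence interval for iCBIT minus placebo, one week after treatment (week 11), lies below 0.

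The section closes with a contingency: if the model does not converge, which the protocol calls unlikely, "an analysis of covariance with last observation carried forward will be carried out instead". This is a stated rule, not a detail left open for the analysis plan.

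Three other places bear on it. The Introduction says efficacy is hard to show "due to the natural waxing and waning course of tics". The Study Design section states "The drop-out rate is expected to be less than 10" per cent, with no figure by arm. In the Schedule of Assessments, the only post-randomisation tic assessment before week 11 is at week 5.

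**The concern.** LOCF treats a patient's last score as the week-11 score. With this visit schedule, only two values can be carried. A patient lost before week 5 gets a change of exactly 0. A patient lost after week 5 gets the week-5 change, about halfway through treatment. Neither is a natural guess at week 11 in a fluctuating disorder in which both arms may improve.

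The planned mixed model uses all observed scores and is valid when data are missing at random. The fallback replaces that assumption with a frozen-score assumption, although the problem being solved is only numerical. The estimate then depends on how many patients each arm loses, and when.

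The direction cannot be foreseen. The Blinding section expects patients to work out their arm, which could push placebo patients to leave. The Compliance section offers later iCBIT only to patients who complete their allocated treatment, which could keep them in. At stake are the type I error of the superiority claim if placebo loses more patients, and power if iCBIT does.

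**Working it through.** **The plan's own figures.** From the Sample Size Calculation: "we expect a mean difference of 3.0 instead of 3.5 for the sample size estimation"; the source studies' result "was 3.5 (±5.5 SD), when comparing face-to-face CBIT to psychoeducation"; one-sided 2.5%; 72 per arm for 90% power. A noncentral-t calculation gives 90.2% at 72 per arm and 89.8% at 71, so 72 is reproduced. It gives 84.2% at 60 and 87.0% at 65 per arm, close to the stated 84–86%.

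**Assumptions for the LOCF check** (not in the documents): placebo improves by 3 points at week 11; half of any change is reached by week 5; dropout is unrelated to scores within an arm; visit correlation is 0.5. A share *e* of losses occurs before week 5. Negative differences favour iCBIT.

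**Formula.** For an arm with mean week-11 change *m* and loss *p*, the expected LOCF change is (1 − p)m + p(1 − e)m/2 = m[1 − p(1 + e)/2]. The standard error of the difference is 5.5 × √(2/72) = 0.917.

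**No true difference (m = −3 in both arms).** The bias is 3 × (1 + e)/2 × (p_iCBIT − p_placebo). One-sided error is Φ(−1.96 + |bias|/0.917) when the bias favours iCBIT, and Φ(−1.96 − |bias|/0.917) when it does not.

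| Loss iCBIT / placebo | Bias, e = 0.5 | Bias, e = 1 | One-sided error |
|---|---|---|---|
| 10% / 10% | 0 | 0 | 2.5% |
| 5% / 10% | −0.11 | −0.15 | 3.3% to 3.6% |
| 0% / 10% | −0.23 | −0.30 | 4.3% to 5.1% |
| 10% / 5% | +0.11 | +0.15 | 1.9% to 1.7% |
| 10% / 0% | +0.23 | +0.30 | 1.4% to 1.1% |

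If every loss falls after week 5 (e = 0), the biases are half those at e = 1: 0.075 and 0.15 points.

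A simulation (two-sample test on change, 40,000 replicates) agrees. It gives 3.2% and 3.6% for 5% / 10%, and 4.3% and 5.1% for 0% / 10%. With equal 10% loss it gives 2.4–2.5%, so with equal loss and no true difference the error rate is not inflated.

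The bias scales with the assumed improvement. For 5% / 10% with all losses early, it is 2 × 0.05 = 0.10 points (error 3.2%) for a 2-point improvement, and 5 × 0.05 = 0.25 points (4.6%) for a 5-point improvement.

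**True effect of 3 (m = −3 placebo, −6 iCBIT).**
- Equal 10% loss: −3 × [1 − 0.1(1 + e)/2] = −2.85, −2.78 and −2.70 for e = 0, 0.5 and 1. Power is about 84–87%.
- The fair comparator is 72 × 0.9 ≈ 65 completers per arm, with 87.0% power.
- Loss of 10% on iCBIT and 5% on placebo, e = 1: −6 × 0.90 + 3 × 0.95 = −2.55. Power is Φ(2.55/0.917 − 1.96) = 79%.
- Loss of 5% on iCBIT and 10% on placebo, e = 1: −6 × 0.95 + 3 × 0.90 = −3.00. The two biases cancel.

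**How likely is the trigger?** A random-intercept REML model was fitted to simulated data for 144 patients. It used the listed fixed effects, baseline rows of exactly 0 and up to 10% loss. It converged in 200 of 200 runs, and in 60 of 60 in a repeat, with no zero variance estimate (statsmodels rather than SAS).

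**The case against.** The strongest reply is that the clause will probably never be used. It is pre-specified, so it cannot be picked after seeing results. The main analysis is likelihood-based, and further sensitivity analyses are promised. Expected dropout is low, and the stated rate appears alongside a follow-up of 6 months, so loss by week 11 should be lower still. The biases above are a fraction of the 0.92 standard error, and some are conservative. All of this stands, and it limits the weight of the point.

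It does not remove the point. The protocol names the estimator that would decide superiority, and an analysis plan choosing another would contradict it. Pre-specification prevents selective choice but does not make the estimator unbiased. Losses of 5% / 10% and 0% / 10% average 7.5% and 5%, both inside the protocol's overall expectation.

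Three stronger readings are tempting:
- *Non-convergence is likely*, because baseline is a time point at which every change is 0, so an unstructured covariance would be singular. The protocol specifies a random patient effect and no unstructured covariance, and that model remains estimable.
- *LOCF cuts power from 90% to 84%.* This compares 10% loss with no loss. Against 65 completers per arm, the cost is at most about 3 points.
- *The fallback would also favour iCBIT in the non-inferiority comparison.* Shrinkage towards 0 could do so, but the Secondary Analyses section says only that the model follows the primary one, not that the fallback carries over.

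**Conclusion.** The point holds as a conditional one. If the mixed model fails to converge, the confirmatory test rests on a frozen-score assumption that does not fit the protocol's own account of tics. The estimate is then generally biased under unequal dropout, and shrunk towards 0 under equal dropout with a real effect.

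With dropout up to 10% per arm, the one-sided error could rise from 2.5% to between about 3% and 5% if placebo loses more patients. It falls below 2.5% if iCBIT does. Those figures rest on the assumed 3-point improvement in both arms, on the timing of losses, and on the fallback being triggered at all. Nothing in the document shows the trigger to be probable. The change is worth making because it is cheap and strictly improves the contingency, not because the trial's error rate is in serious danger.

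**What to change.** Replace the last sentence of the Primary Analysis section with an ordered fallback:

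1. If the model does not converge, refit a simpler or re-specified likelihood model to the post-baseline visits only (week 5 and week 11), for example compound symmetry with a robust (sandwich) variance, with baseline score as a covariate.
2. If that also fails, use ANCOVA of the week-11 change after multiple imputation by arm, with baseline and week-5 scores in the imputation model.
3. Keep LOCF at most as a sensitivity analysis.

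The same sentence can say whether the sequence also applies to the non-inferiority comparison. The cost is one sentence and a little programming. The 72 per arm and all other stated figures are unchanged.
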